### Data storage and analyses

#### Data storage

The specific individual-level and community-level data collected in the study are shown in Tables 1 and 2, respectively.

Participants will be assigned a unique study identification number that will used when recording all individual-level data about the participant. To protect the identify of participants, all identifying information about participants (name, national ID number, telephone number, date of birth, address, etc.) will not be included in electronic databases for the project but, rather, kept in paper documents (with the unique study identification number) held in a secure location at each of the 17 research centers.

All paper-based forms and all data directly entered on computers or tablets at the local clinics or the regional hospitals will be safely transferred to secure locations or password-protected computers at the coordinating research centers as soon as is practical. All data recorded on paper forms will be checked by two researchers prior to entry on a database to minimize missing data. At each of the 17 research locations a standalone password protected computer will be used to enter and store hardcopy coded data and to store all softcopy data. All data will be stored and preserved in a designated secured and locked space, available only to the assigned data manager and his/her assistants at each research site.

#### Storage and primary analyses of biological samples and MRI image

A total of 15 ~ 20 ml venous blood, 10 ~ 15 ml fresh urine, 1 g fresh faeces and 20 hairs over 3 cm will be obtained from each participant. These biological samples will be centrifuged at local laboratory and aliquoted for long-term storage in ultra-cryogenic refrigerator of -80 °C. Part of the blood, hair, urine and stool samples will be used for biochemistry, genomics, metabolomics and gut microbiome analysis. The residual sample materials will be carefully stored and analyzed when needed.

All raw images from MRI scans will be transferred to the Second Xiangya Hospital, where analyses of images, data processing and storage will be performed. High resolution structural 3D-T1 images will be collected and brain morphology including whole brain volume, gray matter volume, white matter volume, thickness, and surface area will be assessed. Resting-state fMRI images will be used to describe the spontaneous functional activity and connectivity of neurons. Diffusion tensor imaging (DTI) data will be used to assess the microstructure of white matter. Data from these primary analyses will be uploaded into the management system and stored at the local password protected computer. In the future, these raw data will be available for additional analyses.

#### Data analyses

Three main analyses will be conducted. P values of < 0.05 will be considered statistically significant.

The first set of analyses will describe the characteristics of participants and the detailed epidemiology of depression, including the prevalence, incidence, regional characteristics, and trends in the demographic characteristics of depression over time. Means and standard deviations will be used to describe continuous variables, and numbers and percentages will be used to describe categorical variables. Poststratification weights will be used to estimate the national prevalence and incidence of depression. Latent variable analyses and disease trajectory analyses will be used to describe the changes of depressive disorders over time.

The second set of analyses will 1) identify risk factors that influence the onset, severity and course of depressive disorders; 2) identify characteristics that can help distinguish distinct subtypes of depression; and 3) assess potential pathophysiological mechanisms that link the different types of factors associated with depression – external environmental factors, social factors, psychological factors, and biological factors. T-tests, analyses of variance, Kruskal–Wallis tests and Chi-square tests will be used to analyze differences between groups. Correlation analyses will be used to check correlations between variables. To identify potential risk factors for depression, Cox regression analyses will be used to estimate the hazard ratios (HRs) of the association of specific bio-psycho-social risk factors with the diagnosis of depression. Logistic and liner regression will be used to identify factors associated with the severity or depressive episodes. Genomic analysis (including GWAS analysis, Mendelian Randomization), metabolomic analysis and gut microbiome analysis may also be used to explore potential biological mechanisms of depression.

The third set of analyses will use the findings about risk factors to generate and test different prediction tools of depression. Different predictive models will be generated using machine learning algorithms, including Support Vector Machine, Decision Tree and Random Forest algorithms [37, 38]. Performance of the different models will be compared using the area under the receiver operating curve, prospective prediction results (sensitivity, specificity, accuracy, positive predictive value, negative predictive value) and decision curve analysis (DCA) [38].

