**OTHER MEASURES** Standard questionnaires and self-report questionnaires, some of which are designed by project researchers Participants come to local health clinic and complete the questionnaires online	31. **Occupation:** Occupation type, working intensity, job satisfaction
	32. **Lifestyle:** Smoking, drinking, exercise, habit, pets and etc
	33. **Childhood exposures:** Raised up by who, family background at childhood, abuse or bullying received as a child or adolescent and etc. Additionally, Child Trauma Questionnaire will be used
	34. **Utilization of mental health services:** Knowledge and demand of mental health services, how many times do participants actually use this resource
	35. **Life events:** Major events in life such as divorce, death of close relatives or friends, and etc. Additionally, Life Events Scale will be used
	36. **Childbearing history (for women):** This variable is designed especially for women, including menstruation, pregnancy, miscarriage, and etc

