
**Table 2 Tab2:** Environmental level variables at each of the 34 study communities

TYPE OF DATA Source of data Collection method	Variables
**CLIMATE** Official website of China Meteorological Administration Researchers record data for the 34 sites each season each year	1. **Temperature:** Lowest, highest, and average temperature per season
	2. **Precipitation:** Lowest, highest, and average precipitation per season
	3. **Sunshine:** Lowest, highest, and average time of sunshine per season
	4. **Climate alert:** Types and frequencies of climate alerts per season
	5. **Natural disasters**: Intensity and duration of natural disasters, including floods, forest fires, earthquakes, mud-rock flow, and typhoons
**NATURAL ENVIRONMENT** Official website and annual report of Ministry of Ecology and Environment Researchers record data for the 34 sites each season each year	6. **Noise:** Days noise level exceeds standard level, average intensity of noise, type of noise
	7. **Atmospheric environment:** Lowest, highest and average level of air pollution index (e.g., PM 2.5, SO_2_), average days air quality rated as ‘good’ or better
	8. **Water environment:** Water quality and nutrition index of main rivers and lakes
	9. **Soil environment:** Amount and quality of cultivated area
	10. **Radiation:** Intensity of ionizing radiation and electromagnetic radiation
	11. **Pollution:** Amount and type of waste discharged into the environment, including but not limited to solid waste, car exhaust, industrial waste
**SOCIOECONOMIC CHARACTERISTICS** Official website of National Bureau of Statistics and China Statistical Yearbook Researchers calculate socioeconomic indexes based on data provided in the two sources	12. **GDP index:** Total and per capita GDP
	13. **Aging index:** Proportion of population aged over 60 years old
	14. **Poverty gap** Proportion of population living below local poverty level

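### A single p < 0.05 rule is stated without exception for an analysis section that includes GWAS, metabolomic and microbiome work, and it cannot serve for those screens

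*Protocol article*

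**What the plan says.** The Data analyses section of the protocol article opens with "Three main analyses will be conducted" and then gives the rule: "P values of < 0.05 will be considered statistically significant". No exception, adjusted threshold, false discovery rate or family-wise control is named there or elsewhere in the article.

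The three sets that follow differ in kind:

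- The first is mainly descriptive: characteristics of participants, prevalence, incidence and trends.
- The second holds the hypothesis tests. It says that "Cox regression analyses will be used to estimate the hazard ratios (HRs) of the association of specific bio-psycho-social risk factors with the diagnosis of depression", and it also covers severity, course, subtypes and mechanisms. It ends: "Genomic analysis (including GWAS analysis, Mendelian Randomization), metabolomic analysis and gut microbiome analysis may also be used to explore potential biological mechanisms of depression".
- Prediction tools built from the risk-factor findings make up the third. On their evaluation it says: "Performance of the different models will be compared using the area under the receiver operating curve, prospective prediction results", followed by decision curve analysis.

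The section on storage and primary analyses of biological samples commits part of the samples to genomic, metabolomic and microbiome assays. The Discussion expects newly identified biomarkers to support subgroup-specific drugs and other interventions.

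**The concern.** A threshold of 0.05 means that one null test in twenty is called significant. That is tolerable for a few named hypotheses. It is not tolerable for a screen of thousands to millions of variants, metabolites or taxa, because the expected number of chance hits grows in proportion to the number of tests. The rule sits above all three sets and the omics work sits inside the second, so a reader who follows the text literally would apply 0.05 to a GWAS. The resulting biomarker list would be unusable, and new biomarkers are among the study's stated products.

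This is a stated rule that does not fit the analyses placed under it, which is different from detail left out. The article names no primary hypothesis test to which 0.05 could be confined.

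**Working it through.** **The plan's own figures.** The 0.05 is a convention and has no derivation to reproduce. The one computed statistical figure in the article is the sample size of 79,986 for a 2.1% prevalence with a 95% interval of 2.0% to 2.2%. An exact (Clopper-Pearson) interval of total width 0.002 at 2.1% gives 79,986, so it reproduces. It concerns the precision of a prevalence and gives no power or effect size for any risk-factor or omics test.

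**Inputs.**

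- Threshold: 0.05 (Data analyses).
- Individual-level items: 36 (numbering of Table 1).
- Community-level items: 14 (numbering of Table 2).
- Omics tests: no number given. Assumed: 100,000 to 10 million for a GWAS, and 1,000 metabolites.
- Share of tested factors truly associated (π) and power: not given; varied below.

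**Expected chance findings if all nulls are true** = number of tests × 0.05. **Chance of at least one, if tests are independent** = 1 − 0.95^m.

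| Tests (m) | Expected false positives | Chance of at least one |
|---|---|---|
| 14 | 0.7 | 51% |
| 36 | 1.8 | 84% |
| 50 (36 + 14) | 2.5 | 92% |
| 1,000 (assumed) | 50 | about 100% |
| 100,000 (assumed) | 5,000 | about 100% |
| 1 million (assumed) | 50,000 | about 100% |
| 10 million (assumed) | 500,000 | about 100% |

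Overlap between factors lowers the last column but leaves the expected count unchanged. The 50 is a rough proxy. Some numbered items are not risk factors (item 25 is the PHQ-9, and item 30 is the clinical assessment behind the diagnosis). Others hold many variables: temperature alone is lowest, highest and average in each season, or 3 × 4 = 12 values a year.

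**Share of significant results that are false** = 0.05(1 − π) / [0.05(1 − π) + power × π].

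- π = 0.1%, power 80%: 0.04995 / (0.04995 + 0.0008) = 98%.
- π = 1%, power 80%: 0.0495 / (0.0495 + 0.008) = 86%.
- π = 10%, power 80%: 0.045 / (0.045 + 0.08) = 36%.
- π = 20%, power 80%: 0.04 / (0.04 + 0.16) = 20%.

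The share passes one half only when π is below 0.05 / (0.05 + power). That is 5.9% at 80% power, 9.1% at 50% and 20% at 20%. A very small π is plausible for an agnostic genome-wide screen. Nothing in the article shows it for risk factors chosen beforehand.

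**With a suitable threshold.** For an assumed 1 million tests, 0.05 / 1,000,000 = 5x10^-8 per test. The chance of any false hit is then 1 − (1 − 5x10^-8)^1,000,000 = 4.9%. For 100,000 and 10 million tests the corresponding thresholds are 5x10^-7 and 5x10^-9.

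**The case against.** The best defence is that the omics work is optional and exploratory, since the article says it may be used. Genome-wide thresholds and multiplicity families are also commonly left to a full protocol or analysis plan, which is not shown. Both points are fair. The absence of omics detail is no finding, and the optional wording limits how serious this is. Neither rescues the sentence: it is stated without exception, and a later document that set a genome-wide threshold would have to override it.

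A second defence is that p < 0.05 is compatible with adjusted p values. It is, but the article does not say that the values will be adjusted. If that is the intention, stating it would largely answer the point.

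A reader might infer more than the text supports, in three ways:

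- **That most significant findings of the study would be false.** For the risk-factor analyses this needs a share of true associations below about 6% at 80% power. The documents give neither quantity, and the Introduction and Discussion cite earlier evidence for several candidates, such as air pollution and childhood maltreatment.
- **That all 50 listed items are screened against every outcome.** The article applies Cox models to specific factors and describes no such screen.
- **That the prediction models are built on chance findings.** The third set draws on the risk-factor findings but states no selection by p value. It compares models by discrimination, prospective prediction results and decision curves.

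The first set is mainly descriptive, so the rule matters chiefly in the second.

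**Conclusion.** The point holds for the omics and other agnostic screens. As written, 0.05 would call about 5,000 to 500,000 null variants significant over an assumed 100,000 to 10 million tests, and about 50 of an assumed 1,000 null metabolites. These counts rest on assumed numbers of tests, but no plausible number makes 0.05 workable for a GWAS.

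For the candidate risk factors the consequence is modest: some chance findings, about 2.5 if 50 factors were each tested once and all were null. Whether these would be a large part of the significant results cannot be settled from the documents. Statisticians differ on whether formal multiplicity control is needed there in an exploratory cohort. The change is worth making because it is cheap and the omics part of it is uncontroversial.

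**What to change.** Replace the single sentence with a short paragraph that does the following:

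- Says that 0.05 does not govern the omics screens, and limits it to any tests named in advance as primary.
- States a genome-wide threshold for GWAS, for example 5x10^-8.
- States false discovery rate control, for example Benjamini-Hochberg at 5%, within each metabolomic family, each microbiome family, and each imaging family that is run as an agnostic screen.
- Says that other risk-factor associations are reported as estimates with confidence intervals and labelled exploratory unless named in advance as primary.

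The cost is one paragraph, with no change to sampling or data collection. The downside is fewer nominal discoveries from the omics screens.

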#### Enrollment and baseline evaluation

Residents of the 34 primary sampling sites who meet the inclusion and exclusion criteria will be randomly selected from lists of community members registered in the public health system (described above) and invited to participate in the project. To improve the response rate, prior to the enrolment advertising billboards will be set up at the local health service center and messages introducing the study will be sent to all community members via WeChat (social media) site. Enrollment and baseline data collection included the following steps (see Fig. 2):A)Basic information (e.g., name, age, address, phone number) of residents in the community is extracted from the community health service center (which typically have a registry of virtually all permanent residents in each community).B)Among the permanent residents 18 years of age or older, 3250 individuals will be randomly selected from the registry of residents maintained by the local health authorities.C)Researchers make phone calls to selected residents to introduce the China Depression Cohort Study-I and – if the individual expresses interest in participating – to invite them to the local community health service center for an intake interview. Researchers and community health care workers will make home visits to invite individuals who cannot be contacted by phone.D)When potential participants visit the community clinic they will be provided with details about the project and asked to sign a written informed consent.E)Baseline assessments of consenting participants are typically conducted at the local health clinic on the same day as enrollment. They include the following:Community clinic physicians conduct a physical exam, measuring weight, height, heart rate and blood pressure.Research nurses collect biological samples of blood, urine and faeces.Trained researchers instruct participants in the use of the online Participant Module and supervise their completion of self-report questionnaires about their demographic characteristics, environmental exposures, and mental health symptoms.Community clinic doctors conduct a psychological evaluation using the expanded version of the 12-item General Health Questionnaire (GHQ-12) [34, 35], which consists of the original Chinese version of the GHQ-12, and 12 additional items to improve its sensitivity. The 12 supplemental items include 6 items described in previous studies [34, 36] (respondents' subjective report of their physical health in the past month; respondents' subjective report of their psychological health in the past month; obsessive thoughts or compulsive behaviors in the last month; restriction of activities because of phobias in the past month; feelings of extreme nervousness or anxiety in the last six months; and social problems due to drinking in the last year), and 6 items developed for the current project based on expert consultation (feeling depressed or down for at least two weeks; seeking help from others due to psychological problems; hospitalization due to psychological problems; suicidal behaviors such as self-poisoning or self-injury; intention of self-harm or suicide; family history of mental disorders such as depression). The 12 GHQ-12 items are each scored as 0 (not present or mild) or 1 (present to a moderate or significant degree); so the total GHQ-12 score ranges from 0 to 12. Each participant will be classified as low-risk of depression (a GHQ-12 score of 0 to 1 and none of the 12 additional items present), moderate-risk of depression (a GHQ-12 score of 2 to 4 and none of the 12 additional items present), or high-risk of depression (a GHQ-12 score of at least 5 or a positive score on any of the 12 additional items) [36].Formal diagnostic examination by a psychiatrist using the SCID-5-CV interview schedule will be conducted in all participants classified as high-risk of depression, in 40% participants classified as moderate-risk of depression and in 10% participants classified as low-risk of depression. Similar to other two-stage epidemiological studies [34, 36], higher proportions of individuals at higher risk of depression are administered the definitive diagnostic interview; this method allows for an efficient use of the limited number of psychiatric personnel available while allowing for accurate prevalence estimates for the total population (by estimating the rates of false positive GHQ-12 rates in the high-risk group and rates of false negative GHQ-12 rates in the moderate- and low-risk groups).All high-risk participants are referred for a brain MRI scan at a regional hospital, and low-risk and moderate-risk participants are given the option of a referral for a brain MRI scan.

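### Comparisons by baseline SCID diagnosis are not tied to the 100%/40%/10% interview fractions, so exposures linked to the screen would be biased if the tests are run as named

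*Protocol article*

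**What the plan says.** Protocol article, Enrollment and baseline evaluation: the SCID-5-CV interview is held "in all participants classified as high-risk of depression, in 40% participants classified as moderate-risk of depression and in 10% participants classified as low-risk of depression". A participant is high-risk with a GHQ-12 score of 5 or more, or with "a positive score on any of the 12 additional items". One of those items is "family history of mental disorders such as depression"; others cover social problems due to drinking and self-rated physical health. The section justifies the two-stage design as "allowing for accurate prevalence estimates for the total population".

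Protocol article, Data analyses, first set: "Poststratification weights will be used to estimate the national prevalence and incidence of depression".

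Same section, second set (risk factors, subtypes, mechanisms): "T-tests, analyses of variance, Kruskal–Wallis tests and Chi-square tests will be used to analyze differences between groups". Correlation analyses and logistic and linear regression are also listed, and Cox regression is named for hazard ratios of risk factors. P below 0.05 counts as significant. No weight or screening stratum is mentioned for this set, the groups are not defined, and the handling of participants without a SCID interview is not stated.

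**The concern.** At baseline the SCID diagnosis is known only for a subset drawn with very unequal probabilities, and those probabilities depend on the screening result. The screen is meant to be related to depression, and it contains variables that are themselves candidate risk factors. When selection into the analysed set depends on both the exposure and the disorder, an ordinary test in that set addresses association among the interviewed, not in the cohort.

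The protocol allows for this when it estimates prevalence but does not carry it over to group comparisons. Poststratification weights in the usual sense align a sample with known population margins. The screening class has no known national margin, so these weights do not undo the 100/40/10 sampling.

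At stake are baseline contrasts on family history, drinking problems, physical health and anything correlated with the screen. A null factor could look protective, and a modest real one could vanish or reverse.

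**Working it through.** **The plan's own figure.** The documents give no figure for the group tests. The one computed figure nearby, 79,986 for a 95% interval of 2.0% to 2.2% at 2.1%, is reproduced exactly by the Clopper-Pearson interval. It concerns prevalence precision and does not bear on this point.

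**Inputs from the protocol.** N = 85,000; prevalence 2.1%; interview fractions 1.0, 0.4 and 0.1; any added item puts its carrier in the 1.0 class.

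**Assumptions, not in the protocol.** 5% of people carry the item. Screen performance through the other items is varied below. Individuals are treated as independent, so clustering within communities is left out.

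**Formula.** Carriers are always interviewed. A non-carrier is interviewed with probability f = 1.0·P(high) + 0.4·P(moderate) + 0.1·P(low), called fD if depressed and fN if not. Hence the OR among the interviewed = true OR × fN/fD.

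For a screen with high/moderate shares of 80%/15% in cases and 20%/30% in non-cases:
- fD = 0.80 + 0.4×0.15 + 0.1×0.05 = 0.865
- fN = 0.20 + 0.4×0.30 + 0.1×0.50 = 0.370
- fN/fD = 0.43

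**A null item (true OR 1), unweighted, interviewed subset:**

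| Assumed high/moderate, cases vs non-cases | fD | fN | OR | chi-square | p |
|---|---|---|---|---|---|
| 80/15 vs 20/30 | 0.865 | 0.370 | 0.43 | 62.8 | 2e-15 |
| 60/25 vs 20/30 | 0.715 | 0.370 | 0.52 | 36.5 | 1.5e-9 |
| 80/15 vs 5/20 | 0.865 | 0.205 | 0.24 | 199.7 | 2e-45 |
| 50/25 vs 40/30 (weak) | 0.625 | 0.550 | 0.88 | 1.3 | 0.25 |
| uninformative | 0.370 | 0.370 | 1.00 | 0 | 1 |

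Check of row 1 by counts:
- Carriers: 4,250, of whom 89 are depressed (2.1%).
- Non-carriers: 80,750, of whom 1,696 are depressed and 79,054 are not.
- Interviewed non-carriers: 1,696×0.865 = 1,467 depressed and 79,054×0.370 = 29,250 not, so 4.8% depressed.

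Item prevalence of 2% or 10% leaves the OR in row 1 unchanged and gives chi-square 26 or 118.

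**True effects, rows 1 and 2:**
- True OR 1.5 appears as 0.64 and 0.78 (p = 1.6e-6 and 0.007): reversed.
- True OR 2 appears as 0.86 and 1.04 (p = 0.06 and 0.68): hidden.
- True OR 3 appears as 1.28 and 1.55: right direction, attenuated.

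**Un-interviewed coded as non-cases.** Observed prevalence in non-carriers becomes 0.021×fD. At fD = 0.865 this is 0.0182, and a null item shows OR 1.16 (p = 0.18). At fD = 0.715 the OR is 1.41 (p = 0.002), and at 0.625 it is 1.61 (p = 1.5e-5). The bias runs upward.

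**Simulation, 1,000 cohorts per case, null exposure, nominal 5%** (row 1 screen unless stated; Monte Carlo standard error √(0.05×0.95/1,000) = 0.7 points):

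| Exposure | Unweighted mean OR, rejection | Weighted 1/2.5/10 mean OR, rejection |
|---|---|---|
| Screening item | 0.43, 100% | 1.00, 4.3% |
| Screening item, weak screen | 0.87, 21% | 0.99, 5.9% |
| Not an item, doubles odds of screening high | 0.83, 34% | 0.99, 6.2% |
| Unrelated to screening | 0.99, 4.7% | 0.99, 7.5% |

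Weighting works because it restores the full counts. For depressed non-carriers, 0.80×1×1 + 0.15×0.4×2.5 + 0.05×0.1×10 = 1.

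**The case against.** The article does not say that the tests are unweighted, that the groups are SCID cases against non-cases, or that un-interviewed people are dropped. The groups could be depression subtypes. It is a condensed article, its authors plainly understand two-stage sampling, and details of weighting are often left to an analysis plan. This limits the point to comparisons that use baseline SCID diagnosis. It does not remove it: the article does address weights, attaches them to one set of analyses, and names ordinary tests for another.

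A reader might infer three stronger things that the documents do not support:
- **That screening items will generally come out significant in the wrong direction.** This needs an informative screen and analysis of the interviewed only. With a weak screen the bias is small, with an uninformative one it is absent, and with un-interviewed people coded as non-cases it runs the other way. Strong effects keep their direction. Several added items, such as two weeks of low mood or psychiatric hospitalisation, are symptoms or consequences of illness, so a null effect is not realistic for them.
- **That the whole risk-factor aim fails.** Cox regression is the named tool for hazard ratios of risk factors, and follow-up ascertainment does not use the 100/40/10 scheme.
- **That the prediction tools inherit the error.** They build on risk-factor findings for which Cox regression is named, and are judged partly on prospective prediction.

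**Conclusion.** The point holds in limited form. For comparisons by baseline SCID diagnosis, the tests as named do not match the sampling that produced the diagnosis, and neither unweighted handling of un-interviewed participants is valid under an informative screen. Among the interviewed, the OR of a screening item is multiplied by about 0.4 to 0.5 if 60–80% of cases and 20% of non-cases otherwise screen high-risk, and by about 0.9 under a weak screen. This gives a spurious inverse association for a null item and can hide or reverse a true OR of 1.5 to 2. A variable that only correlates with the screen is affected less (OR 0.83 in the case examined). An exposure unrelated to screening is not biased. The mechanism follows from the protocol's own rules; the size rests on screen performance that the protocol does not give. The Cox analyses of incident depression lie outside this conclusion.

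**What to change.** Under Data analyses, state that:

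1. Comparisons, correlations and regressions that use baseline SCID diagnosis as outcome or grouping variable are weighted by the inverse of the achieved SCID fraction in the participant's risk class (design values 1, 2.5 and 10).
2. They use design-based tests: Rao-Scott chi-square, and weighted regression with sandwich variance.
3. Un-interviewed participants are not counted as non-cases in these analyses.

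The cost is plan wording and standard survey procedures. No new data are needed, since every participant is assigned a risk class. The downside is somewhat larger standard errors, because low-risk participants carry weight 10. In the first scenario only about 1,696×0.05×0.1 = 8 low-risk cases would be interviewed among non-carriers. The weighted test can then be slightly liberal (7.5% in the unrelated-exposure case), so the number of cases behind each weight should be reported beside the result.
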